**Methods:**

A multicenter, randomized, assessor-blinded clinical trial will be conducted. One hundred forty-two participants will be recruited by eligibility criteria and be randomly divided into two groups. The intervention group will receive thread-embedding acupuncture in addition to electroacupuncture, while the control group will be given only electroacupuncture. The primary outcome is a change in the physical function score of the Facial Disability Index. The secondary outcome is change in Sunnybrook Facial Grading System, Social/Wellbeing function score of Facial Disability Index, Synkinesis Assessment Questionnaire, Numeric Rating Scale of stiffness by facial region, Patient Global Impression of Change, Euro-Qol 5-Dimension 5-level, Economic evaluation questionnaire and adverse events. Assessment points include before treatment (Week 1), after treatment completion (Week 6), 2 weeks post-treatment completion (Week 8, Primary endpoint), and 10 weeks post-treatment completion (Week 16).

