### Sample size calculation

2.4

The level of significance (*α*) is set at 0.05 (two-sided test). Type II error (*β*) is set at 0.2, with a test power of 80%. No clinical trial of thread embedding with the same design could be found through a literature review. Therefore, the sample size was calculated by applying the mean difference of 9.29 and the standard deviation of 17.146 for the Facial Disability Index’s Physical score as the primary efficacy evaluation indicator, based on the results of previously conducted, similar clinical trials on the sequelae of FNP (10).

Considering a dropout rate of 20% (11), 71 participants per group will be needed. A total of 142 participants will be assigned to the study: 71 persons per group, with 102 patients (51 in the TEA group, 51 in the control group) at the one medical center and 40 patients (20 in the TEA group, 20 in the control group) at the other medical center. If an institution’s recruitment ends early, additional participants will be recruited competitively to ensure a smooth enrollment process.

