### Statistical analysis

2.9

Statistical analysis will be performed using the Full Analysis Set (FAS) analysis group, which includes participants who have received treatment at least once, and missing values will be addressed using multiple imputations. All statistical analyses will be based on two-sided tests, with a significance level set at 5%. The SAS version 9.1.3 statistical package (SAS Institute, Cary, NC, USA) will be used as the analytical tool. Descriptive statistics will be provided for each group concerning the demographic characteristics and baseline clinical data of the participants. Comparisons between groups will be conducted using the independent t-test, the Wilcoxon rank-sum test for continuous data, and the Chi-square test or Fisher’s Exact test for categorical data. For the analysis of secondary efficacy evaluation variables in Weeks 6 & 16 (secondary endpoint), the same method as the primary efficacy evaluation variables will be used. The paired t-test or Wilcoxon signed-rank test will also be employed to analyze the differences in pre- and post-treatment measurements within each group. The repeated measured Analysis of Variance (repeated measures ANOVA) will be used to assess the interaction between time and group over time.

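### The planned repeated-measures ANOVA relies on sphericity if run uncorrected, and it gives no Week 8 arm difference; a mixed model would do better (minor)

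*Protocol article*

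**What the plan says.** The primary outcome is the change in the Facial Disability Index (FDI) physical function score. The abstract's Methods paragraph lists assessments before treatment (Week 1), at the end of treatment (Week 6), and then "2 weeks post-treatment completion (Week 8, Primary endpoint), and 10 weeks post-treatment completion (Week 16"). Table 1 marks the same four visits for the index and labels Week 8 as the primary endpoint.

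Section 2.9 (Statistical analysis) compares the groups by independent t-test or Wilcoxon rank-sum test and applies the primary variable's method to Weeks 6 and 16. It then adds the longitudinal analysis: "The repeated measured Analysis of Variance (repeated measures ANOVA) will be used to assess the interaction between time and group over time". For incomplete data it says that "missing values will be addressed using multiple imputations", in a full analysis set of participants treated at least once. The error level covers every test: "All statistical analyses will be based on two-sided tests, with a significance level set at 5"%.

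The section does not say whether the F test is univariate or corrected, and it does not call the interaction supportive.

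**The concern.** The classical univariate group-by-time F test holds its level only under sphericity: the difference between any two visits must have the same variance whichever pair is taken. Here one score precedes treatment and three follow it, two of them only two weeks apart. Scores close together, or on the same side of treatment, usually correlate more strongly than the others, so the condition is unlikely to hold. An uncorrected test would then reject too often, against the 5% that the section sets for all analyses.

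The test is also not very informative for this trial. It is a single test on 3 degrees of freedom over all four visits. A small p-value says only that the two profiles differ somewhere. It gives neither the Week 8 difference nor a confidence interval for it, although the trial is sized on a two-group mean difference.

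**Working it through.** **Inputs from the document.** Alpha "is set at 0.05 (two-sided test"); beta "is set at 0.2, with a test power of 80"%; "the mean difference of 9.29 and the standard deviation of 17.146"; "Considering a dropout rate of 20% (11), 71 participants per group will be needed". Visits at Weeks 1, 6, 8 and 16.

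**Inputs assumed.** The document gives no correlations or variances over the visits. I used compound symmetry (r = 0.5), serial correlation with a weekly value of 0.80 to 0.99, and one pattern with the SD rising from 1.0 to 1.4.

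**1. The plan's sample size.**
- Normal formula: n = 2 × [17.146 × (1.960 + 0.842) / 9.29]² = 53.5, so 54 per arm; 54 / 0.8 = 67.5, so 68.
- Exact t-test: 55 per arm (power 0.804); 55 / 0.8 = 68.75, so 69.

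The stated 71 is close and slightly conservative. After 20% dropout, 71 × 0.8 = 56.8, so I simulated 57 per arm.

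**2. Why sphericity is implausible.** With serial correlation, Var(difference) = 2σ²(1 − ρ^gap). At a weekly ρ of 0.95:
- Weeks 6 and 8 (gap 2): 2σ²(1 − 0.9025) = 0.195σ².
- Weeks 1 and 16 (gap 15): 2σ²(1 − 0.463) = 1.07σ².

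The ratio is about 5.5; sphericity needs 1.

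**3. False-positive rate of the interaction test.** The uncorrected F has 3 and 3 × (114 − 2) = 336 degrees of freedom. Departure from sphericity is measured by ε = (tr M)² / [3 tr(M²)], where M is the covariance matrix of three orthonormal visit contrasts; ε = 1 is sphericity. There were 20,000 null trials per row, so the Monte Carlo standard error is √(0.05 × 0.95 / 20,000) = 0.15 percentage points.

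| Pattern | ε | Uncorrected F | Greenhouse-Geisser | Week 8 t-test on change |
|---|---|---|---|---|
| Compound symmetry, 0.5 | 1.00 | 5.3% | 5.1% | 5.3% |
| Weekly 0.80 | 0.87 | 5.7% | 4.6% | 5.2% |
| Weekly 0.90 | 0.78 | 6.4% | 5.0% | 5.1% |
| Weekly 0.95 | 0.72 | 6.7% | 4.9% | 4.9% |
| Weekly 0.97 | 0.69 | 6.9% | 5.0% | 4.9% |
| Weekly 0.99 | 0.66 | 7.3% | 5.1% | 5.2% |
| Weekly 0.95, rising SD | 0.65 | 7.0% | 4.9% | 5.2% |

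Two further simulations with assumed correlations gave 6.0% to 7.2% and 5.9% to 7.7% uncorrected, and 4.9% to 5.2% and 4.6% to 5.2% corrected.

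**4. Is unequal spacing the cause?** With equally spaced visits (Weeks 1, 6, 11, 16), weekly correlations of 0.95 and 0.90 gave 6.5% and 6.2% uncorrected. The planned visits gave 6.7% and 6.4%. Spacing is not the cause; unequal correlation is.

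**The case against.** The strongest reply is that an epsilon correction, a covariance structure and a pooling rule commonly sit in a statistical analysis plan, which is not shown, and that this is a condensed article. That stands: a missing correction is not in itself a fault, and the uncorrected test is one reading of the text. What remains is that the article names a method that carries an avoidable assumption and does not return the quantity of interest. It can also be said that the interaction test was never asked for the Week 8 difference. That is fair, and it is why the point is minor.

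Four stronger readings are tempting, and the document supports none of them.

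- **That the trial's false-positive rate rises to about 9%.** If success could be claimed on either the Week 8 t-test or the interaction test, the rate would be 8.6% to 10.7% uncorrected and 8.0% to 9.0% corrected (two independent tests: 1 − 0.95² = 9.75%). The protocol contains no either-test rule. It names one primary outcome at one time point.
- **That unequal visit spacing invalidates the test.** Visit can be a categorical factor, and equal spacing gives nearly the same excess.
- **That the analysis cannot be combined with multiple imputation.** The interaction is a set of contrasts with estimates and a covariance matrix, and multi-parameter pooling rules give one test across imputed data sets.
- **That a fifth of participants would be lost.** A completers-only analysis would keep about 142 × 0.8 = 114, but the section plans the full analysis set with imputation.

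Nor is it a defect that an omnibus test and a Week 8 contrast sometimes disagree (6% to 15% of trials in simulations with a real effect). They answer different questions.

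**Conclusion.** The point holds in a limited form. Run as an uncorrected univariate F test, the interaction analysis would probably exceed the document's 5% level, at about 6% to 8% under non-spherical patterns with ε of roughly 0.65 to 0.87. The lower end of that range barely departs from 5%. These figures rest entirely on assumed correlations and on the uncorrected form of the test; a standard correction removes the excess.

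The Week 8 t-test is unaffected, at 4.9% to 5.3% in every pattern for the planned visits. The lasting weakness is that repeated-measures ANOVA gives no arm difference with a confidence interval at Week 8 or any other visit. Severity is minor.

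**What to change.** Replace repeated-measures ANOVA with a mixed model for repeated measures on Weeks 6, 8 and 16, in the planned analysis set. Include arm, visit, arm by visit, baseline score by visit, and centre, with an unstructured covariance. Report the arm difference with its confidence interval at each visit. If multiple imputation is kept, each difference has an estimate and a standard error, so the ordinary pooling rules apply. At minimum, keep the ANOVA with a Greenhouse-Geisser correction and name a multi-parameter pooling rule.

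Add one sentence stating that the Week 8 FDI physical-score comparison alone is confirmatory and that the interaction and the other visits are supportive.

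Baseline adjustment also gains precision. With equal variances, an unadjusted change score has variance 2σ²(1 − ρ) and an adjusted score σ²(1 − ρ²), a ratio of (1 + ρ)/2. For an assumed baseline correlation of 0.3 to 0.6, the adjusted variance is 65% to 80% of the unadjusted one.

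The cost is revised wording and a different SAS procedure, with no new data. The change should be fixed before results are seen; section 2.1 expects data collection to finish by November 30, 2025.

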### Data collection and management

2.10

Participants and clinical trial information will be documented in the electronic medical record (EMR) system of the medical institution. Data collection, management procedures, and information on blinding will be provided only to designated researchers who will handle and crosscheck the trial data. Evaluation records completed by patients and assessors will be kept confidential and maintained as supporting evidence, recorded in both the EMR and paper, and subsequently entered into an electronic case report form (eCRF) provided by MyTrial (Bethesda Soft Co., Ltd., Seoul, Korea). Researchers will be assigned role-based permissions to access, modify, and input data within the eCRF system, with all activities logged for accountability.

### Quality control

2.11

The study procedures and documentation will be periodically monitored according to the Korean Good Clinical Practice guidelines.

## Discussion

3

In this multi-center, randomized controlled trial protocol, we aim to evaluate the effectiveness and safety of TEA alongside electroacupuncture for FNP. Adhering to the SPIRIT and STRICTA guidelines, our methodologically rigorous study design will extend previous research by utilizing a larger, diverse cohort, meticulous inclusion and exclusion criteria, and a comprehensive range of primary and secondary outcome measures.

To overcome the limitations of a previous clinical trial and design a trial applicable to clinical practice, we conducted a preliminary survey targeting Korean medical doctors with clinical experience in performing TEA for FNP. The survey revealed that 29-gauge mono-needles were most commonly employed to mitigate contracture between the lips and nasolabial folds. TEA session numbers averaged 5.9 per patient, with few instances surpassing 20 needles (20). Considering these usage trends, we established TEA administration sites, intervals, and quantities.

This study will use electroacupuncture as the control group to restore paralyzed nerves and muscles (21). According to reviews of earlier animal studies, electroacupuncture treatment favors the expression of elements involved in nerve regeneration (22–24). The results of the aforementioned survey showed that roughly 60 practitioners are using TEA treatment along with electroacupuncture (20), which has been clinically confirmed through systematic literature reviews (25, 26). Electroacupuncture, with these effects, is employed in clinical settings to treat acute symptoms and sequelae of facial paralysis along with acupuncture or TEA.

Beyond its role in FNP, acupuncture intervention holds significant importance across various diseases, particularly in neurological and brain cognitive disorders. Recent advanced works have highlighted the profound modulatory effects of acupuncture on neural diseases and brain cognition, employing a range of sophisticated measurements to evaluate its effectiveness. For instance, studies have demonstrated neural activation via acupuncture in patients with major depressive disorder, as evidenced by functional near-infrared spectroscopy (27). Furthermore, acupuncture’s efficacy in modulating brain activity has been evaluated using periodic-aperiodic EEG measurements (28), and its impact on spectral power and functional connectivity in the human brain has been meticulously investigated (29). Acupuncture therapy has also shown promising effects on patients with mild cognitive impairment, as observed through functional near-infrared spectroscopy (30). The development of neural manifold decoders for acupuncture stimulations, employing representation learning, further underscores the intricate interaction between acupuncture and the brain (31). These findings collectively suggest that acupuncture serves as a clinically important intervention across a spectrum of diseases, extending far beyond localized conditions.

The potential mechanisms by which acupuncture, and specifically the combined TEA and electroacupuncture treatment in our protocol, act on FNP are multifaceted. Electroacupuncture, as supported by existing literature, promotes the expression of neurotrophic factors such as Nerve Growth Factor (NGF), Ciliary Neurotrophic Factor (CNTF), and Glial Cell-Derived Neurotrophic Factor (GDNF) (21), thereby facilitating the regeneration of damaged facial nerves. It also improves Schwann cell morphology and supports neuronal survival and growth, contributing to the recovery of paralyzed muscles and the alleviation of sequelae such as synkinesis (22–24). Thread Embedding Acupuncture, on the other hand, involves the subcutaneous insertion of absorbable threads that provide continuous physical and biochemical stimulation. This leads to improved local circulation, enhanced collagen formation, and modulation of inflammation, all of which contribute to tissue regeneration (32–34). The synergy between electroacupuncture and TEA in our protocol aims to create an optimal biochemical environment for nerve regeneration, induce electrical activity in paretic muscles, and leverage unique acupuncture-specific responses, such as the “Deqi” sensation, to modulate central and peripheral nervous systems, thereby maximizing therapeutic outcomes.

This randomized controlled trial is designed to delve deeper into the implications of this study protocol. While acute FNP treatments are often well-standardized, long-term sequelae such as synkinesis, contracture, spasm, and crocodile tears syndrome present a significant clinical challenge with limited and often insufficiently evidenced treatment options, including nerve transplantation or botulinum toxin injections. To assess whether the sequelae have been resolved, it is crucial to consider both the perception of physical changes and self-recognized improvements in functional areas (35). In this study, we will conduct a comprehensive evaluation using the physician-rated Sunnybrook Facial Grading System (SFGS), as well as patient self-assessments via the Facial Disability Index (FDI) and Numeric Rating Scale (NRS).

The upcoming randomized controlled trial aims to examine the effectiveness and safety of TEA combined with electroacupuncture in managing FNP. This study, designed to address previous research limitations, will use rigorous methodologies and an adequate sample size. The objective is to explore TEA’s potential benefits, disadvantages, and possible adverse events to uncover improved therapeutic strategies.

The potential applications of the findings from this study will extend significantly into clinical practice and future research. If proven effective and safe, TEA could offer a new, minimally invasive therapeutic option for patients suffering from long-term FNP sequelae. Furthermore, the successful validation of TEA in this context could stimulate broader research into its applications for various other health conditions. For instance, TEA could be explored as a rehabilitation treatment for post-stroke hemiplegia or other neurological motor disorders, chronic musculoskeletal pain syndromes, or neuropathic pain management, leveraging its continuous stimulatory effects. In the cosmetic field, it could complement existing facial aesthetic acupuncture techniques to enhance skin elasticity, reduce wrinkles, and correct facial asymmetry. This study, therefore, not only aims to establish evidence-based standards for TEA in treating FNP but also serves as a crucial foundation for strengthening the scientific validation of complementary and alternative medicine, thereby expanding our understanding and utilization of TEA for a diverse range of health concerns.
